## **Artesunate – Amodiaquine - Methylene blue – Phase II Clinical Trial Protocol**

haemoglobin during follow-up (Müller et al. 2013). Given the strong *in vitro* and *in vivo* effect on *P. falciparum* gametocyte reduction (Adjalley et al. 2011, Coulibaly et al. 2009), the potential synergy with artemisinin drugs (Akoachere et al. 2005), and the low potential for resistance development, MB has been considered a potentially useful partner drug for artemisinin-based combination therapies (ACT), particularly in regions where elimination is the final goal (Müller et al. 2009). This is supported by the findings from the first MB-ACT trial conducted in 2011 in Burkina Faso (Coulibaly et al. 2015).

### **Primaquine**

8-aminoquinolons are chemically related to methylene blue (MB) and seem to function through a NADPH oxidation process (Rosenthal 2000). However, how exactly primaquine (PQ) works is unknown.

PQ is the only registered drug against the hypnozoites of *P. vivax* and is also effective against the asexual forms and the gametocytes of this parasite. However, it is not widely used in endemic areas due to serious adverse events when given at high dose and/or for a prolonged time to patients with G6PD deficiency (Recht et al. 2014). In particular, the potential of PQ to cause life-threatening drop of haemoglobin levels is feared, which may occur when the G6PD activity is below 10% (Recht et al. 2014). Although G6PD prevalence in SSA is high (ranging from 5-30% in the male population), the prominent G6PD deficiency type in SSA (A-) usually has a high residual enzyme activity and is thus not considered very dangerous (Bousema & Drakeley 2011, Recht et al. 2014).

In areas of low malaria transmission, it was formerly recommended that a single dose of primaquine (0.75 mg base/kg; 45 mg adult dose) be added to ACT in acute falciparum malaria to block malaria transmission. Review of studies of transmission-blocking activity based on the infectivity of patients or volunteers to anophelid mosquitoes, and of haemolytic toxicity in G6PD deficient subjects, suggests that a lower primaquine dose (0.25 mg base/kg) would be safer and equally effective. WHO now recommends that this lower dose can be deployed together with ACTs without G6PD testing wherever use of a specific gametocytocide is indicated (Recht et al. 2014).

## **4 Trial objectives and purpose**

The overall goal of the underlying research project is to develop a MB-based first-line drug combination regimen against uncomplicated falciparum malaria in SSA.

The primary objective of this study is:

- To study the safety of the triple combination AS-AQ-MB compared to AS-AQ-PQ in the treatment of uncomplicated falciparum malaria in young African children

The secondary objective of this study is:

- To study the efficacy of this MB-based triple combination in comparison with standard ACT-PQ in the treatment of uncomplicated falciparum malaria in young African children

*Justification:* ACT combined with single low-dose PQ is the standard regimen used against falciparum malaria in areas where transmission reduction is the main goal. There is *in vitro* and *in vivo* evidence for MB acting synergistic with artemisinin drugs by both altering the redox system of *P. falciparum*. Moreover, there is also *in vitro* and *in vivo* evidence for MB acting against both the young and the old stages of gametocytes. Increased efficacy of the antimalarial regimen would likely also reduce gametocyte production. Finally, adding MB to standard ACTs may further protect the artemisinin component against resistance development by its independent modes of action together with the lowering of transmission of pre-resistant parasites.

## **Definition of outcomes**

### Primary endpoint:

- Change in haemoglobin values on day 7 of follow-up compared to baseline

### Secondary endpoints:

- *P. falciparum* gametocyte prevalence and density on days 1, 2, 3, 7, and 28 of follow-up (microscopic determination)
- The area under the curve of *P. falciparum* gametocyte density versus time
- Incidence of observed and self-reported adverse events over the 28 days observation period
- Fever and parasite clearance time
- Haematological recovery, i.e. haemoglobin concentrations during follow-up
- Adequate clinical and parasitological response (ACPR) as assessed by microscopy rate (PCR-corrected for recrudescences) over a 28 days observation period
- Rates of early treatment failures (ETF), late treatment failures (LCF) and late parasitological failures (LPF) (PCR-corrected for recrudescences) over the 28 day observation period
- Acceptance of the different treatment regimens by mothers/caretakers assessed on day 14

## **5 Design of the trial**

The study is designed as a mono-centre, two-arm randomised controlled phase II non-inferiority study in north-western Burkina Faso. As MB leads to blue urine, the study will be open label but with blinding for the laboratory technicians who are responsible for haemoglobin measurements and parasite determination in blood smears and PCR samples (observer blinded study).

### Study procedures:

100 children aged 6-59 months with uncomplicated falciparum malaria will be included into the study. All study children will be followed up for 28 days.

## **Artesunate – Amodiaquine - Methylene blue – Phase II Clinical Trial Protocol**

After all data have been collected, double entered and cleaned at the study site, the database will be closed. Data analysis will be carried out in Germany through independent statisticians. Report writing and publication will take place in Burkina Faso and Germany involving key researchers from all collaborating partners. Finally, the policymakers in Burkina Faso will be informed through specific workshops and the implications of the study results on the respective malaria control policies will be discussed.

All study procedures will be conducted according to Good Clinical Practice (GCP) guidelines.

The study will take place in the study area of the CRSN in Burkina Faso, where highly experienced staff (physicians, nurses, fieldworker, and laboratory technicians) for the conduct of clinical studies is already available.

Children will become recruited from Nouna town. Fever measurement points will become established in a rotating manner in the different quarters of the town. Children found eligible for the study will be transferred to the study unit in the Nouna Hospital for further examination and final inclusion into the study.

### **Randomisation and blinding**

The randomisation numbers will be allocated to the two groups using the random number generator of the validated software SAS®. Sealed envelopes are produced and labelled with the randomization number. Inside of the sealed envelope, a data sheet defines the group allocation of the patient with the respective randomization number. On enrolment in the study, each patient receives the randomisation envelope in consecutive order of inclusion in the study. Basic characteristics of the patient and day of randomisation are documented on the data sheet in order to allow a check whether the randomization scheme was strictly observed.

Due to the colouration of urine through MB, blinding of patients is not possible. However, all lab technicians examining the blood samples for haemoglobin values, malaria parasites and other study-relevant aspects will be blinded to treatment regimen.

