### **Sample size**

The sample size calculation is based on the primary comparison of the mean change in haemoglobin (day 7 – baseline) between the two treatment groups. 50 patients per arm are needed to assess non-inferiority of AS-AQ-MB to AS-AQ-PQ with a power of 80% at a one-sided significance level of 2.5%, with allowance for 10% loss to follow-up and with the use of a clinically relevant non-inferiority margin of  $\delta=0.7$ , assuming a standard deviation of 1.1722 in both groups (estimate based on own unpublished data from Coulibaly et al. 2015). Thus, the overall number of study patients is 100. Sample size calculation was performed using ADDPLAN v6.1.

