### **Drug storage and drug accountability**

The investigator, or his designated deputy (e.g. nurse or pharmacist), will make sure that the Investigational Products are adequately stored in a secured area with restricted access, under recommended storage conditions by the manufacturer and in accordance with applicable regulatory requirements. Prior to dispensing, all study medications should be stored by the investigator between 20 °C and 30 °C. The investigator must record the receipt and usage of all drugs supplied.

A drug accountability utilisation log will be maintained for clinical trial material by the investigator. This will include the date and time of administration, the quantity administered and the patient randomisation number. The log should be signed and dated by the investigator.

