## **10 Trial monitoring and auditing**

Clinical Monitoring will be performed by a qualified physician from the National Malaria Research Institute in Ouagadougou, Burkina Faso, an institution which is independent from other trial staff to ensure patient safety and integrity of the clinical data, e.g. primary endpoint in adherence to study protocol. Regular on-site monitoring visits are planned depending on the recruitment rate and quality of the data. The investigator must allow the

monitor to have access to all essential documents and source data and must provide support at all times to the monitor. Existence, informed consent, age and body weight of patients, SAEs and haemoglobin values at baseline and at day 7 will be monitored 100%.

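### The record used to check the randomisation order is kept on the sheet sealed with the allocation, so it can show envelopes used out of sequence but not that the child was fixed before the arm was seen

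*Protocol*

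**What the plan says.** Section 5 of the protocol (Randomisation and blinding) sets out the allocation procedure:

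- **Outside of the envelope:** "Sealed envelopes are produced and labelled with the randomization number". Nothing else is said to be written there.
- **Inside:** "Inside of the sealed envelope, a data sheet defines the group allocation of the patient with the respective randomization number".
- **Order rule:** "each patient receives the randomisation envelope in consecutive order of inclusion in the study".
- **Check on the order:** "Basic characteristics of the patient and day of randomisation are documented on the data sheet in order to allow a check whether the randomization scheme". The date is recorded to the day, with no clock time.

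Three other places bear on the point:

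- **Section 5, opening paragraph:** "As MB leads to blue urine, the study will be open label but with blinding for the laboratory technicians". Treating staff therefore know the arm once it is assigned.
- **Section 6, Drug storage and drug accountability**, on the log kept by the investigator: "This will include the date and time of administration, the quantity administered and the patient randomisation number".
- **Section 10:** "Existence, informed consent, age and body weight of patients, SAEs and haemoglobin values at baseline and at day 7 will be monitored 100" per cent. Envelopes and allocation order are not among the items named.

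**The concern.** Concealment depends on the child being irrevocably linked to the next number before anyone can see what that number holds. The protocol states a safeguard and its purpose, but puts the record on the one document that cannot be reached without breaking the seal. The linking entry is thus made after the allocation is known.

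The opportunity is realistic. Children are found at fever measurement points in the town and transferred to one hospital unit (section 5, Study procedures), so two may be waiting together. Prognostic information is at hand: baseline blood is taken directly after consent (Definitions), and a haemoglobin below 7 g/dl excludes (Exclusion criteria), so the value must be known to confirm eligibility.

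The primary comparison is the difference in mean haemoglobin change from baseline to day 7. If the choice of child depended on the visible arm, a difference in prognosis between the groups would enter that contrast. Blinding the laboratory technicians guards against measurement bias, not against this.

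**Working it through.** **1. Which record exists when.**

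| Record | Content | Made before the seal is broken? |
|---|---|---|
| Envelope label | Randomisation number | Yes, but no patient is named |
| Data sheet | Allocation, basic characteristics, day | No, it lies inside the envelope |
| Drug accountability log | Date and time of administration, quantity, randomisation number | No, it follows dosing |

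No record in the protocol is both made before opening and carries a patient identifier next to the number.

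**2. What the check can and cannot show.** Suppose two eligible children, A and B, are waiting on the same day. Staff open the next envelope, see the arm, and enter B. A then receives the following envelope. Both sheets carry consecutive numbers and the same date, and the drug log shows the numbers dosed in order. Nothing looks wrong. By contrast, an envelope skipped on one day and used on a later day would show in the dates, and one used out of order within a day might show in the drug-log times.

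**3. How often the day alone leaves the order open.** Assume 100 children enrolled at random over D recruitment days. The share who have at least one other child on the same day is 1 − (1 − 1/D)^99:

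- D = 155: 47%
- D = 125: 55%
- D = 90: 67%
- D = 60: 81%

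The protocol gives only the study period, June to November 2016, so D is an assumption.

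**4. The plan's own sample size.** The inputs are a margin of 0.7, an SD of 1.1722 and 10% loss, "with a power of 80% at a one-sided significance level of 2.5" per cent. The normal formula gives 2 × (1.96 + 0.8416)² × 1.1722² / 0.7² = 44.02, so 45 per arm. The t-based power at 45 is 0.800, and 45 / 0.9 = 50. The stated 50 per arm is reproduced and is not in question.

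**5. Illustration of size.** Assumptions: 45 evaluable per arm; true difference at the margin; a share s of envelopes in each arm given to the better-looking (MB) or worse-looking (primaquine, PQ) of two children; correlation ρ between staff's judgement of prognosis and haemoglobin change; every steered choice favours MB. The better of two standard normal values has mean 1/√π = 0.564, so

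- shift in contrast = 2 × s × ρ × 1.1722 × 0.564
- standard error = 1.1722 × √(2/45) = 0.247
- one-sided error = P(Z > 1.96 − shift/0.247)

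| s | ρ | Shift (g/dl) | Error, formula | Error, simulation (6,000 runs) |
|---|---|---|---|---|
| 10% | 0.3 | 0.040 | 3.6% | 3.6% |
| 10% | 0.5 | 0.066 | 4.5% | 4.7% |
| 20% | 0.3 | 0.079 | 5.1% | 5.0% |
| 20% | 0.5 | 0.132 | 7.7% | 7.4% |

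The simulated shifts at 10% were 0.040 and 0.064. If the steering ran against MB, the sign reverses: at 10% the error would fall to 1.7% (ρ = 0.3) or 1.3% (ρ = 0.5), and the cost would be lost power.

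**The case against.** The case for leaving the plan as it stands runs as follows.

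- **The protocol does not permit the manoeuvre.** Envelopes go out in consecutive order of inclusion, and opening first and choosing afterwards would breach that. This is true, but the point is whether a breach could be seen.
- **There are other controls.** An independent monitor has access to all source data, and a list of items checked in full does not exclude checking envelopes. Baseline values are compared between groups, and a regression adjusting for baseline haemoglobin is planned (section 9). This stands. However, the adjusted model is additional to the confirmatory test, and it corrects only for baseline haemoglobin, not for other aspects of clinical state.
- **A site procedure may already require an earlier entry.** It may; the protocol is silent. But this is more than detail left out, because the protocol does say where the checking record is kept.

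Stronger readings are tempting and should be resisted. A reader might infer that the check cannot detect steering at all, or that order within a day cannot be checked. Neither is supported: dated sheets expose out-of-order use across days, the recorded characteristics allow the treated child to be matched to the sheet, and the drug log gives a clock-time sequence by randomisation number.

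A reader might also take swapped children to differ by a full SD in expected change. Swapping 10% per arm would then give 2 × 0.10 × 1.1722 = 0.234 g/dl, a third of the margin, and an error near 16%. That treats the total outcome SD as something staff can foresee. Two random children differ in actual change by 1.13 SD on average, so a foreseeable gap of 1 SD for a typical pair needs a correlation of about 1/1.13 = 0.89. It also needs every swap to favour MB, and the protocol gives no reason to expect one direction. With the same shift against MB, the error would be about 0.2%.

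**Conclusion.** The point holds in a limited form. The described check can show envelopes used out of sequence. It cannot show that the child was fixed before the allocation was seen, because the linking entry is on the sheet sealed with the allocation and no earlier record is described.

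The size and direction of any resulting bias are unknown. With 10% of envelopes steered, always towards MB, and correlations of 0.3 to 0.5, the shift is about 0.04 to 0.06 g/dl and the one-sided error at the margin about 3.6–4.7% instead of 2.5%. These figures rest wholly on assumed behaviour and show only what an undetected breach could do.

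This is a misplaced safeguard that is cheap to put right. A reader might take it as a sign that allocation was, or would be, manipulated; nothing in the protocol supports that. Sample size, margin and analysis are unaffected.

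**What to change.** In section 5 (Randomisation and blinding), state that after consent and confirmed eligibility the enrolling staff write the patient identifier, date and clock time on the outside of the next sealed, opaque envelope, or in a sequential enrolment log, and sign before opening it. Keep the opened envelope with its data sheet.

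In section 10, add to the monitored items a reconciliation of envelope number against that date and time and against the first-dose time in the drug accountability log.

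The cost is a label on 100 envelopes and one more item for the monitor. If the site already keeps such a record, it is enough to describe it in the protocol and add the reconciliation.

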### **Duration of the trial**

The study will be implemented between June and November 2016. Follow-up of study subjects will be 28 days.

## **6 Detailed study procedures**

### **Study area**

The area is located in the Nouna Health District in rural north-western Burkina Faso. The study area is highly endemic for malaria, with most transmission taking place during and shortly after the rainy season, which usually lasts from June until October. The area is populated mainly by subsistence farmers of the Bobo and Marka ethnic groups. Study children will be recruited from the outpatient department of the district hospital in Nouna town. The field work will be coordinated by the *Centre de Recherche en Santé de Nouna* (CRSN), which is situated in Nouna town. The laboratory work will be conducted in the laboratory of the CRSN.

### **Sample size**

The sample size calculation is based on the primary comparison of the mean change in haemoglobin (day 7 – baseline) between the two treatment groups. 50 patients per arm are needed to assess non-inferiority of AS-AQ-MB to AS-AQ-PQ with a power of 80% at a one-sided significance level of 2.5%, with allowance for 10% loss to follow-up and with the use of a clinically relevant non-inferiority margin of  $\delta=0.7$ , assuming a standard deviation of 1.1722 in both groups (estimate based on own unpublished data from Coulibaly et al. 2015). Thus, the overall number of study patients is 100. Sample size calculation was performed using ADDPLAN v6.1.

### **Inclusion criteria**

- 6-59 months old children (male and female)
- Weight  $\geq 6$  kg
- Uncomplicated malaria caused by *P. falciparum*
- Asexual parasites  $\geq 2\,000/\mu\text{l}$  and  $\leq 100\,000/\mu\text{l}$
- Axillary temperature  $\geq 37.5^{\circ}\text{C}$  or a history of fever during the last 24 hours
- Burkinabe nationality
- Permanent residence in the study area with no intention of leaving during the surveillance period
- Written informed consent of parents or care takers

### **Exclusion criteria**

- Severe malaria (WHO 2000)
- Mixed malaria infection

## **Artesunate – Amodiaquine - Methylene blue – Phase II Clinical Trial Protocol**

- Vomiting ( $\geq 3$  times within 24 hours before the visit)
- Any apparent significant disease, including severe malnutrition
- A history of a previous, significant adverse reaction or known allergy to one or more of the study drugs
- Anaemia (haemoglobin  $< 7$  g/dl)
- Treated in the same trial before
- All modern antimalarial treatment prior to inclusion (last seven days)
- Therapy with serotonin reuptake inhibitors (e.g. citalopram, escitalopram, fluoxetine, Paroxetine, Sertraline)
- Simultaneous participation in another investigational study
- Treatment with other investigational drugs
- Patients with known HIV/AIDS disease
- Therapy with drugs known to inhibit the liver enzymes cytochrome 2A6 (e.g. methoxsalen, pilocarpine, tranlycypromine) and/or cytochrome 2C8 (e.g. trimethoprim, ketoconazole, ritonavir, saquinavir, lopinavir, gemfibrozil, montelukast)

### **Withdrawal criteria**

Participants may be withdrawn from the study at their guardians' request. In case of vomiting after the repeated drug intake (one repetition only) of the first drug ingestion, the participant will be withdrawn from the study.

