#### **Methylene blue**

Methylene blue (MB) is a water-soluble dye used for a long time in industry and medicine. In humans, the drug is rapidly and widely distributed throughout the body (Schirmer et al. 2003; Wainwright & Amaral 2005; Schirmer et al. 2011). The drug is well absorbed from the gastrointestinal tract and partly monodemethylated to azure B in hepatocytes. Maximal plasma concentrations are reached 2 hours following oral administration, and the plasma half-life is about 20 hours (Walter-Sack et al. 2009). Renal excretion of MB and azure B (in oxidised blue or reduced uncoloured forms) is the main elimination pathway (DiSanto and Wagner 1972, Peter et al. 2000). Known side effects of MB are a bitter taste, a mild and self-limiting dysuria, and a blue colouration of the urine (Schirmer et al. 2011, Müller et al. 2013). In contrast to its obvious toxicity when applied intravenously at doses >10 mg/kg, the oral application of MB is usually well tolerated. Even oral doses up to 17 g (5x 100-200 mg per day) were well tolerated

in early malaria studies (Guttmann and Ehrlich 1891). In a historical case series of 40 children with malaria from Brazil, oral doses of 20-50 mg/kg per day given over days to weeks have also been well tolerated (Ferreira 1893).

MB has been used against malaria for more than 100 years (Guttmann und Ehrlich 1891, Ehrlich 1913). Its further use against human malaria is not well documented, thus only observational data supported its efficacy, particularly in malaria cases found refractory to quinine (Ehrlich 1913, Dale 1956). MB is a registered drug in most countries for a number of indications such as treatment of methaemoglobinaemia (Schirmer et al. 2011). It is also used for the prevention of ifosfamid-induced encephalopathy in human cancer treatment. For these indications, MB is usually given intravenously 2-6 times per day at a dose of 1-2 mg/kg (Mansuri and Lurie 1993, Zulian et al. 1995, Aeschlimann et al. 1998, Pelgrims et al. 2000). The use of MB in malaria treatment may also be beneficial in preventing methaemoglobinaemia and thus tissue hypoxia (Anstey et al. 1996). Another potentially clinically relevant effect is an increase in blood pressure in patients with septic shock due to a blockade of NO-dependent guanylate cyclase (Galili et al. 1997).

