### **Procedures for monitoring subject compliance**

Drug intake will be directly observed and assisted by the study nurses or specific field staff for the whole treatment period. In case of vomiting within 1/2 hour after first drug ingestion, the treatment dose will be repeated. In case of further vomiting, the child will be withdrawn from the study and treated according to local standards.

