## **9 Statistics**

### Analysis sets

The primary efficacy analysis will be based on the full analysis set (FAS) according to the intention-to-treat (ITT) principle, reflecting the recommendations given in guidelines (e.g. ICH Harmonised Tripartite Guideline, 1999). Furthermore, in 2005 Brittain and Lin demonstrated that the ITT and the per-protocol (PP) set yield almost identical results. Thus, ITT should be preferred as the primary efficacy set here. Additionally, an evaluation of the primary outcome will be performed in the PP set, in accordance to Snapinn in 2000, where the importance of the PP set in non-inferiority trials was emphasised. Before database closure the assignment of each patient to the PP and the ITT population are defined in the statistical analysis plan.

The safety set will consist of all patients who received one of the study treatments at least once, and patients will be allocated to the treatment they actually received. This will be the primary analysis set for the safety analysis.

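### A child who vomits the repeated first dose leaves the study, not only study drug, so day-7 haemoglobin and later adverse events are not collected and the primary outcome must be imputed

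*Protocol*

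**What the plan says.** Two places in section 6 of the protocol state the rule. Procedures for monitoring subject compliance begins: "In case of vomiting within 1/2 hour after first drug ingestion, the treatment dose will be repeated". It continues: "In case of further vomiting, the child will be withdrawn from the study and treated according to local standards". Withdrawal criteria has the same consequence: on vomiting after the one permitted repeat "of the first drug ingestion, the participant will be withdrawn from the study". Both end participation in the study. Neither says that any outcome is still measured.

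Other sections assume that outcomes are measured:

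- Section 4, Definition of outcomes, sets the primary endpoint: "Change in haemoglobin values on day 7 of follow-up compared to baseline".
- Section 5, Study procedures, has all study children followed for 28 days.
- Period of observation of adverse events runs from consent to the final examination on day 28.
- Section 9, Analysis sets: "The primary efficacy analysis will be based on the full analysis set (FAS) according to the intention-to-treat (ITT) principle". The safety set holds every child who received a study treatment at least once. Assignment of patients to the ITT and PP sets is left to the SAP.
- Section 9, Confirmatory analysis, replaces a missing primary outcome by multiple imputation, with treatment group and baseline haemoglobin as covariates. Complete-case analysis and ICA-r are named as examples of sensitivity analyses.

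**The concern.** The trigger acts on the first dose. At that point both arms take artesunate-amodiaquine and only the experimental arm takes MB, because primaquine is not given until day 2. A reaction to MB can therefore set off the rule and a reaction to primaquine cannot. If withdrawals are commoner under MB, the arms lose children unequally after randomisation, in a trial whose primary objective is safety.

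Two things are lost for each such child. The first is the day-7 haemoglobin, which is the primary outcome. An analysis plan can choose how to impute it but cannot recover a value that the protocol never collected. The second is adverse events from withdrawal to day 28. The child stays in the safety-set denominator while observation has stopped, so the frequencies planned under Safety analysis would miss later events.

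**Working it through.** **The plan's own sample size.** Inputs from section 6, Sample size: margin 0.7, SD 1.1722, one-sided 2.5%, power 80%, 10% loss. The true difference is not stated and is taken as 0.

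n per arm = 2 × [1.1722 × (1.960 + 0.842) / 0.7]² = 44.02, so 45. Allowing for loss, 45 / 0.90 = 50 per arm. This reproduces the plan. Noncentral-t power at 45 per arm is 80.0%.

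**Power with extra losses in the MB arm only.** Assume that these come on top of the full 10% loss in both arms. SE = 1.1722 × √(1/n_MB + 1/45), noncentrality = 0.7 / SE, degrees of freedom = n_MB + 45 − 2.

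| Extra MB losses | n_MB vs n_PQ | SE | 0.7 / SE | Power |
|---|---|---|---|---|
| 0 | 45 vs 45 | 0.2471 | 2.833 | 80.0% |
| 1 | 44 vs 45 | 0.2485 | 2.817 | 79.5% |
| 2 | 43 vs 45 | 0.2500 | 2.800 | 79.1% |
| 5 | 40 vs 45 | 0.2547 | 2.748 | 77.5% |

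Five children (10% of 50) is an assumption. The protocol gives no rate, and its 10% allowance may already cover such losses.

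**What the imputation can and cannot do.** The stated model uses arm and baseline haemoglobin. A withdrawn MB child is thus given a day-7 value drawn as for an MB child with the same baseline who stayed in. In fact that child has vomited both intakes and moved to local-standard care. Complete-case analysis drops the child, so it too estimates the arm mean from retained children only and does not repair the problem.

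**Illustration of bias, on assumed inputs.** Let a share w of the MB arm and none of the control arm be withdrawn. Let their true mean change be D g/dl worse than that of retained MB children. The estimate then favours MB by w × D. At a true difference equal to the margin, with every other child observed, one-sided type I error = Φ(w × D / SE − 1.960), where SE = 1.1722 × √(1/[50(1 − w)] + 1/50).

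| w | D (g/dl) | Bias w × D | SE | Type I error |
|---|---|---|---|---|
| 5% | 0.5 | 0.025 | 0.2375 | 3.2% |
| 5% | 2 | 0.10 | 0.2375 | 6.2% |
| 10% | 0.5 | 0.05 | 0.2409 | 4.0% |
| 10% | 2 | 0.20 | 0.2409 | 12.9% |
| 10% | 0 | 0 | 0.2409 | 2.5% |
| 10% | −1 | −0.10 | 0.2409 | 0.9% |

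The last two rows matter as much as the others. With D = 0 there is no bias. With D negative, for instance because little MB was absorbed, the bias runs against MB. Nothing in the protocol fixes w or D.

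**The case against.** A reader might infer that the rule removes MB-intolerant children from the primary endpoint and contradicts the intention-to-treat analysis. The protocol does not support that, for four reasons.

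- **The children are not removed from the analysis sets.** The primary analysis is on the "full analysis set (FAS) according to the intention-to-treat (ITT) principle", with imputation for missing values. Anyone who received a study treatment stays in the safety set.
- **Intolerance to MB is an inference.** The rule is worded identically for both arms, both take artesunate-amodiaquine at the first dose, and febrile children with malaria may vomit anyway. The exclusion criterion removes only those with three or more vomits in the preceding 24 hours. The Methylene blue section says "Known side effects of MB are a bitter taste" and adds dysuria and blue urine; vomiting is not listed. The protocol also gives MB with food to improve acceptability.
- **The tolerability event itself is not lost.** The vomiting falls within the adverse-event observation period and can be recorded. What goes missing is what follows.
- **The trigger is narrow.** It needs vomiting of the first dose and then of its only repeat, so the number may be one or two children or none.

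All of this stands, and it limits the point to missing outcome data of unknown extent. It does not answer why the outcome should go unmeasured. An unknown direction of bias is a reason to observe the value and not to impute it.

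One further objection has weight: keeping these children brings observed values from barely exposed children on other treatment into the primary comparison, which can dilute a real MB effect in a non-inferiority test. That is the usual price of intention-to-treat, and the planned PP analysis addresses it.

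**Conclusion.** The point holds as an inexpensive improvement, not as an essential correction. As written, both withdrawal statements end data collection for a post-randomisation reason that may be commoner under MB. This sits badly with 28-day follow-up of all study children, adverse-event observation to day 28 and a primary intention-to-treat analysis. The planned imputation treats such a child as a typical treated child of the arm.

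The power cost is minor, at most 2.5 percentage points for up to five extra MB losses. Bias could be nil, could favour MB by 0.025 to 0.20 g/dl on the assumed 5% to 10% withdrawal and a 0.5 to 2 g/dl worse course, or could go against MB. These inputs are illustrations and not estimates. That the loss is in fact one-sided, or that the haemoglobin comparison is in fact biased, cannot be concluded from the protocol.

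**What to change.** Reconcile Withdrawal criteria and Procedures for monitoring subject compliance with Study procedures, Period of observation of adverse events and Analysis sets:

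- State in both section 6 paragraphs that this event ends study treatment only, with clinical care left exactly as already written.
- State that scheduled visits, day-7 haemoglobin and adverse-event recording continue to day 28 unless consent is withdrawn.
- Use the observed values in the FAS and safety analyses, and exclude such children only from the PP set.
- Record the reason for stopping study treatment by arm, so that any imbalance can be seen.

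The cost is a short amendment and a few extra visits, using the existing visit schedule and the home visits already planned for missed appointments. The downside is that the FAS will include some barely exposed children, so the FAS and PP results should be read together. Sample size and the clinical rule are unchanged.
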